## 4. Conclusions

This study aims to deepen the understanding of the dose–response relationship of both full-spectrum cannabis oil and THC oil, contributing valuable insights into their physiological and potentially therapeutic effects. The findings may not only clarify the differential impacts of these compounds but also offer a structured framework for future investigations in the area of cannabinoid-based interventions. By establishing methodological guidelines and highlighting key outcome measures, this research could serve as a foundational reference for clinical and experimental studies moving forward.

## Figures and Tables

**Figure 1 jcm-14-07531-f001:**
[figure not shown]
Data collection positioning during assessment moments.

**Figure 2 jcm-14-07531-f002:**
[figure not shown]
CONSORT 2025 Flow Diagram.

**Table 1 jcm-14-07531-t001:** This table summarizes the amount and type of substance used in each intervention arm of the research.

Substance	Intervention Arms				
	CBD + THC 12.50 mg	CBD + THC 18.75 mg	THC 12.50 mg	THC 18.75 mg	IP
Oil 1 THC Full-Spectrum (2.50 mg/mL THC)	4.81 mL	7.22 mL	5.00 mL	7.50 mL	-
Oil 2 Cannabis Full-Spectrum (50 mg/mL CBD + 1.83 mg/mL THC)	0.25 mL	0.37 mL	-	-	-
Oil 3 MCT (70% coconut 30% corn)	-	-	-	-	5 mL
Total (mL)	4.79 mL	7.19 mL	5.00 mL	7.50 mL	5 mL

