## Abstract

**Background/Objectives: ***Cannabis sativa* (CS) exerts its effects through the endocannabinoid system. Although studies have shown limited evidence regarding the plant’s therapeutic efficacy, little is known about the standardization of doses and their corresponding effects. This study aims to analyze changes in muscle electrical activity and cardiovascular hemodynamics before, during, and after administering doses of full-spectrum cannabis and tetrahydrocannabinol (THC) oils. **Methods:** Participants will be assigned to a single group that will undergo five different interventions: CBD + THC at 12.50 mg, CBD + THC at 18.75 mg, THC intervention at 12.50 mg, THC at 18.75 mg, and placebo intervention (PI). The study will enroll healthy, self-reported men and women aged 18 to 50, with no mental health disorders and no exposure to CS in the past six months. Interventions will occur on five randomized days, following three phases: (1) pre-intervention (PRE-IN); (2) intervention (IN)—1 h after oral oil ingestion; and (3) post-intervention (POST-IN)—2 h 30 min after ingestion. At each stage, 2 min of quiet breathing (QB); 2 min with an inspiratory resistance valve (30% of maximal inspiratory pressure—PImax) and expiratory valve (10% of maximal expiratory pressure—PEmax) (VAL); and 4 min of recovery without the valve (REC) were evaluated. Register: RBR-3jsvtbr. **Conclusions:** This study will enhance the understanding of the dose–response effects of full-spectrum cannabis and THC oils and may serve as a model for future research in this field.

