### 2.1. Sample Size and Allocation

The sample size will be determined after a pilot study with five subjects, considering the cardiac output (CO) values as the main variable in intra- and inter-group comparisons through mixed model analysis of the Generalized Estimating Equations (GEE) test. An alpha error of 0.05 with a two-sided distribution and a test power of 80% will be established. Recruitment will be done through convenience sampling, using direct invitations and advertising on social media, posters, flyers on Instagram and WhatsApp, targeting the general population.

Participants will be randomly assigned to a single group, which will undergo five different types of interventions: (1) CBD + THC intervention at 12.50 mg (CBD + THC/12.50 mg), (2) CBD + THC at 18.65 mg (CBD + THC/18.65 mg), (3) THC intervention at 12.50 mg (THC/12.50 mg), (4) THC at 18.65 mg (THC/18.65 mg), and (5) placebo intervention (IP). The order of interventions for each individual will be randomized using the https://www.sealedenvelope.com website for analysis (accessed on 4 September 2025).

To conduct the five research interventions, we will use three different oils. The first is an THC oil with a concentration of 2.50 mg/mL “Naternal Full Spectrum Delta 9 THC”, from (Naternal^®^, Morrisville, NC, USA). The second is a Cannabis oil containing 50 mg/mL CBD and 1.83 mg/mL THC “Lazarus Naturals High Potency Full Spectrum” from (Lazarus Naturals^®^, Seattle, DC, USA). The third, used in the placebo intervention (IP), is an MCT (Medium Chain Triglycerides) oil used as a base for diluting the full-spectrum Cannabis and THC oils, consisting of 70% fractionated coconut oil and 30% corn oil.

During the THC evaluations, the mL dosages will be determined based on the concentration of the product. Similarly, in the evaluations of the CBD + THC intervention, the THC and cannabis oils will be combined to achieve an equal ratio of CBD and THC for each specific dose. In the placebo intervention, all participants will receive a dose of 5.00 mL of MCT. The dosages and corresponding values are detailed in Table 1.

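### Table 1's totals for the two CBD + THC interventions are not the sums of their oils, and the higher dose is 18.65 mg in section 2.1 but 18.75 mg in the abstract and Table 1

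*Protocol article*

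**What the plan says.** Section 2.1 defines five interventions and refers the reader to Table 1 for their dosages. It describes Oil 1 as a "THC oil with a concentration of 2.50 mg/mL" and Oil 2 as containing 50 mg/mL CBD and 1.83 mg/mL THC. For the mixed interventions it says that "the THC and cannabis oils will be combined to achieve an equal ratio of CBD and THC for each specific dose".

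Table 1 gives the volumes. Its column order is CBD + THC lower dose, CBD + THC higher dose, THC lower dose, THC higher dose, placebo.

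- The first oil appears in the four active columns: "Oil 1 THC Full-Spectrum (2.50 mg/mL THC) 4.81 mL 7.22 mL 5.00 mL 7.50 mL".
- The second is used only where the two products are mixed, and its row reads "Oil 2 Cannabis Full-Spectrum (50 mg/mL CBD + 1.83 mg/mL THC) 0.25 mL 0.37 mL".
- For those two mixed columns the bottom row states "Total (mL) 4.79 mL 7.19 mL". In the other three columns the total equals the single oil listed.

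The higher dose has two values. Section 2.1 writes "CBD + THC at 18.65 mg (CBD + THC/18.65 mg" and uses the same 18.65 mg for the THC-only intervention. The abstract writes "CBD + THC at 18.75 mg", and the Table 1 column headings also use 18.75 mg for both products.

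**The concern.** A total cannot be smaller than one of its parts, yet both CBD + THC totals are below the Oil 1 volume printed in the same column. Table 1 is the only place in the article that gives volumes, and section 2.1 relies on it for the dosages. A reader therefore cannot tell from the article how much oil a participant in a combination intervention receives.

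The design turns on this. At each dose level, comparing CBD + THC with THC alone isolates CBD only if the THC amount is the same in both. If the Total row governed preparation, the combination interventions could carry less THC than their THC-only counterparts, and the CBD contrast would be mixed with a THC difference.

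The second conflict, 18.65 against 18.75 mg, is smaller. It nevertheless leaves the upper dose with two stated values, in two of the five interventions, in a study whose stated aim is dose–response.

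**Working it through.** **Inputs.** Volumes are from Table 1. Concentrations are from section 2.1 and repeated in Table 1: Oil 1 has 2.50 mg/mL THC; Oil 2 has 50 mg/mL CBD and 1.83 mg/mL THC.

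**Step 1: volumes.** Total = Oil 1 + Oil 2 (or the single oil given).

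| Intervention | Sum of listed oils (mL) | Printed total (mL) | Gap (mL) |
|---|---|---|---|
| CBD + THC, lower | 4.81 + 0.25 = 5.06 | 4.79 | 0.27 |
| CBD + THC, higher | 7.22 + 0.37 = 7.59 | 7.19 | 0.40 |
| THC, lower | 5.00 | 5.00 | 0 |
| THC, higher | 7.50 | 7.50 | 0 |
| Placebo | 5 | 5 | 0 |

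As a share of the sum, the gaps are 0.27/5.06 = 5.3% and 0.40/7.59 = 5.3%. As a share of the printed total, they are 0.27/4.79 = 5.6% and 0.40/7.19 = 5.6%.

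**Step 2: can rounding or another formula explain it?** Allowing 0.005 mL of rounding in each component, the sums lie in 5.05–5.07 and 7.58–7.60 mL. Oil 1 minus Oil 2 gives 4.56 and 6.85 mL. Solving the volumes exactly, with Oil 2 = dose/50 and Oil 1 = (dose − 1.83 × Oil 2)/2.50:

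| Dose (mg) | Oil 2 (mL) | Oil 1 (mL) | Sum (mL) |
|---|---|---|---|
| 12.50 | 0.250 | 4.817 | 5.067 |
| 18.65 | 0.373 | 7.187 | 7.560 |
| 18.75 | 0.375 | 7.2255 | 7.6005 |

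No route gives both 4.79 and 7.19 mL. The Oil 1 volume for 18.65 mg does round to 7.19 mL, but the matching figure at 12.50 mg is 4.82 mL, not 4.79, so that does not account for the row.

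**Step 3: doses delivered by the listed oil volumes.** THC = 2.50 × Oil 1 + 1.83 × Oil 2; CBD = 50 × Oil 2.

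- Lower: THC = 2.50 × 4.81 + 1.83 × 0.25 = 12.48 mg; CBD = 50 × 0.25 = 12.50 mg.
- Higher: THC = 2.50 × 7.22 + 1.83 × 0.37 = 18.73 mg; CBD = 50 × 0.37 = 18.50 mg. The CBD figure is low because 0.375 mL is printed as 0.37.
- THC only: 2.50 × 5.00 = 12.50 mg and 2.50 × 7.50 = 18.75 mg.

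The component rows therefore agree with the Table 1 headings and with the equal CBD and THC rule to within two-decimal precision.

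**Step 4: doses if the printed totals were the volumes given.** This assumes Oil 2 as listed and Oil 1 reduced to fit.

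- Lower: Oil 1 = 4.79 − 0.25 = 4.54 mL; THC = 2.50 × 4.54 + 1.83 × 0.25 = 11.81 mg, which is 94.5% of 12.50.
- Higher: Oil 1 = 7.19 − 0.37 = 6.82 mL; THC = 2.50 × 6.82 + 1.83 × 0.37 = 17.73 mg, which is 94.5% of 18.75.

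Against the THC-only interventions the THC gap would be 12.50 − 11.81 = 0.69 mg and 18.75 − 17.73 = 1.02 mg. With the component rows it is about 0.02 mg at each level.

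**Step 5: the two dose labels.** (18.75 − 18.65)/18.75 = 0.5%. In the THC-only intervention, 18.65 mg corresponds to 18.65/2.50 = 7.46 mL, against the 7.50 mL listed.

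**The case against.** The strongest reply is that the error sits in two cells of a derived summary row. Anyone measuring oil by oil from the component rows would obtain the doses in the Table 1 headings and would have no need of the totals. The mismatch is also visible to anyone who tried to use them. The article does not say that staff measure from the Total row, and working preparation instructions may exist in a fuller protocol. The 0.5% label difference has no evident effect on any comparison.

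Much of this stands. The THC shortfall in step 4 depends on an assumed use of the Total row, and three of the five totals are correct. A separate preparation sheet is good practice, but an article need not contain one.

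What does not fall away is the contradiction. These are figures the article states wrongly, not details it leaves to another document. They concern administered amounts, in the only table that gives volumes, and nothing else in the article settles which figures are meant. That the component rows agree with the table headings does not help with section 2.1, which defines the interventions with a different upper dose.

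**Conclusion.** The concern holds. The two CBD + THC totals in Table 1 are 0.27 and 0.40 mL below the sums of their oils (5.3% each), and rounding cannot account for this. The higher dose is stated as both 18.65 and 18.75 mg. These findings rest only on addition and on reading the three places side by side.

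The possible bias is conditional. If the printed totals governed preparation and were met by reducing Oil 1, THC in the combination interventions would be about 5.5% below the headings and no longer matched to the THC-only interventions. If the component rows govern, THC is matched to within about 0.02 mg and the CBD contrast is not affected. The calculation takes the labelled oil concentrations as exact. It does not show which dose or volume is intended. No sample-size, power or alpha figure depends on it.

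**What to change.** Reconcile the abstract, section 2.1 and every row of Table 1 against the intended milligrams and the oil concentrations. State one value for the higher dose throughout. Make each entry in the Total row equal the sum of the component volumes that the sponsor confirms. Adding rows to Table 1 for mg of THC and mg of CBD would let a reader verify each column directly. A single preparation sheet giving mL per oil and mg per cannabinoid would be a useful addition, though it need not be in the article.

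The sponsor must decide which figures are intended; this review does not choose between them. If any dosing has already taken place, the sponsor should also confirm from preparation records which volumes were used. The cost of the change is a corrected table and a few corrected lines of text.

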## Abbreviations

The following abbreviations are used in this manuscript:

BMI	Body mass index
CBD	Cannabidiol
COPD	Chronic Obstructive Pulmonary Disease
CS	Cannabis Sativa
ESC	Scalene
FEF_25–75%_	Forced expiratory flow between 25% and 75% of the FVC curve
FEV_1_	Forced expiratory volume in the first second
FVC	Forced vital capacity
GEE	Generalized Estimating Equations
HAM-A	Hamilton anxiety scale
HHb	Deoxyhemoglobin
ICF	Informed consent form
IN	Intervention
MCT	Medium Chain Triglycerides
MVIC	Maximum Voluntary Isometric Contraction
MVV	Maximum Voluntary Ventilation
NIRS	Near-infrared spectroscopy
O_2_HB	Oxyhemoglobin
PARA	Parasternal
PEMáx	Maximum expiratory pressure
PI	Placebo Intervention
PIMax	Maximum inspiratory pressure
POST-IN	Post-intervention
PRE-IN	Pre-intervention
QB	Quiet breathing
RA	Rectus abdominis
REC	Recovery
RMS	Root Mean Square
SaO_2_	Oxygen saturation
SBP	Systolic Blood Pressure
SCM	Sternocleidomastoid
sEMG	Surface electromyography
THC	Tetrahydrocannabinol
tHb	Total Hemoglobin
TSI	Tissue Saturation Index
VAL	Valve
